#### Parent mentor recruitment and training

Potential parent mentors are identified within each early childhood care center by the Head Start staff as parents who have taken on an active or leadership role within the center. They are then recruited to participate on the basis of interest and availability. All parent mentors have a child attending the center and are required to have conversational-level English and Spanish proficiency. Parent mentors are assigned parent mentees after randomization with the expectation that parents mentor up to 14 parents per month.

All parent mentors undergo two-day training by the research staff. The first day of training covers general mentoring skills, such as active listening and supportive feedback, as well as confidentiality and the logistics of the program. The second day of training is specific to the curriculum they are going to use: either the positive deviance curriculum or the *We Can!* curriculum; each curriculum is described in detail in the following section. In regard to the positive deviance arm, the parent mentors themselves are not positive deviants per se; rather, they receive training in how to mentor other parents on the strategies used by positive deviants. Each potential mentor practices presenting portions of the curriculum. Parents participating in the mentor training are compensated for their time. Research staff observe parents during the training, and the final parent mentors are selected on the basis of the observations of research staff. Criteria used to identify candidates are bilingual fluency, engagement in the training, fidelity to the program content, and active listening skills.

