#### Intervention frequency (intensity)

Parent–child dyads randomly assigned to the control arm receive health information from the Head Start center their child is enrolled in per the center’s usual care practice. Parent–child dyads randomly assigned to either parent mentor arm attend a 1-hour monthly meeting with their parent mentor and the other mentees in their mentoring group. (See Table 1 for a list of topics and activities.) The parents in the mentoring arms also receive individualized coaching on their goals for that month via weekly phone, text, or in-person follow-up with their parent mentor. The two intervention arms have 4 months of group meetings and individual mentoring followed by 2 months of individual mentoring on a weekly basis. The focus for the weekly communication is to encourage the identified behavior change and problem-solve through any potential obstacles faced.

**Table 1 Tab1:** Topics covered in the two active intervention arms with the parent mentor–led curricula

Month	Positive deviance-based curriculum	*We Can!* curriculum
1	Creating a healthy home food environment	Overview, content, and structure of program. Motivation for eating well and moving more.
2	Effective communication around feeding and physical activity	Introducing the concept of energy balance
3	Supporting outside play time	Managing “energy in” of energy balance
4	Providing consistency, specifically around snacking	Managing “energy out” of energy balance
5	Individual goal setting, support, and troubleshooting (no community meeting)	Individual goal setting, support, and troubleshooting (no community meeting)
6	Individual goal setting, support, and troubleshooting (no community meeting)	Individual goal setting, support, and troubleshooting (no community meeting)

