### Sample size

Given the growth patterns of preschool-age children, weight maintenance has been recommended as the goal as this will lead to a reduction in adiposity with expected linear growth [27]. For the power calculations, we used a mean BMI z-score of 2.5 with a standard deviation of 0.7 for the baseline measurements, based on a previous trial in a similar popuation [19]. A BMI z-score of 2.5 is equivalent to a mean of 120% of the 95th percentile BMI for age and gender. Weight maintenance at this age leads to roughly a 0.5-unit reduction in BMI z-score over 4–6 months among children with obesity, a clinically meaningful reduction. We assumed a standard deviation of 1.0 for the 0.5-unit change in BMI z-score over 6 months. With these assumptions and to achieve 80% power at an alpha of 0.05, we would need 64 children per group to complete the 6-month assessment to detect this clinically meaningful difference of 0.5-unit reduction in BMI z-score between the two active intervention groups. We did not include a repeated measures correlation coefficient in our sample size calculation. We estimated a roughly 25% dropout rate by 6 months given the mobility of the targeted population, and so we aimed to recruit and enroll 80 dyads per group (240 parent–child dyads in total).

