### Data analysis

Given the relatively high potential for missing data because of attrition in the population enrolled over time, we plan a procedure of multivariate imputation by chained equations. Variables to be included in the multiple imputation model include BMI z-score of the child, child age, gender, family income, and language. This procedure operates under the assumption that the missing data are missing at random. A pattern mixture model will be applied to examine the informativeness of missing outcome data using time at 6 and 12 months to examine interactions with missing data patterns. The results of the pattern mixture model will be incorporated as a fixed effect in the linear mixed model (described below).

Using an intention-to-treat analysis, we will assess the primary outcome of mean change in adjusted BMI z-score at the end of the active period of intervention and use an alpha of 0.05. We will use linear mixed models to analyze the primary outcome of change in adjusted BMI z-score looking at the main effect of randomization group, time, and their interaction by using Wald tests for statistical significance and Akaike information criterion to assess model fit. A cohort variable, defined as the period of enrollment given multiple enrollment periods over the course of the study, will be included as a fixed effect. Baseline BMI z-score will be examined as a covariate. All models will be examined for the normality, homoscedasticity, and linearity of the residuals to ensure that the assumptions of the models are met.

Secondary outcomes will be analyzed by using similar methods, comparing by randomization group. We will adjust all secondary outcomes for multiple comparisons by using the Holm–Bonferroni method. We will track participation with a potential secondary analysis carried out stratifying by levels of participation. All quantitative analyses will be completed by using SPSS software version 24 (IBM Corporation, Armonk, NY, USA).

We will employ three regression equations to complete planned mediation analyses of intervention effects by the secondary outcomes. These include the main intervention effect on the primary outcome, change in adjusted BMI z-score, the main intervention effect on the mediating variables (secondary outcomes), and the combination of the intervention effect and mediating variables on the primary outcome. We will use a product-of-coefficients approach to examine the potential mediators [45].

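### Both arms of the primary comparison are delivered in mentor-led groups, but the primary model as described names no mentor effect and the 64-per-group calculation assumes independent children

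*Protocol article*

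**What the plan says.** Dyads are randomised individually, 1:1:1 (Protocol article, Randomization). The primary comparison is between the two active arms at 6 months (Primary outcome).

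Delivery in both of those arms is by group. Dyads "attend a 1-hour monthly meeting with their parent mentor and the other mentees in their mentoring group" (Intervention frequency), and the same mentor coaches them individually each week. On assignment and load: "Parent mentors are assigned parent mentees after randomization with the expectation that parents mentor up to 14 parents per month" (Parent mentor recruitment and training). The same section gives each mentor a second training day on one curriculum only, so mentors are nested within arm.

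The Data analysis section plans linear mixed models "looking at the main effect of randomization group, time, and their interaction by using Wald tests for statistical significance". It adds enrolment period as a fixed cohort effect, baseline BMI z-score as a candidate covariate and a fixed pattern-mixture term. It lists no random effects of any kind.

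The Sample size section takes a "clinically meaningful difference of 0.5-unit reduction in BMI z-score between the two active intervention groups" and states: "We assumed a standard deviation of 1.0 for the 0.5-unit change in BMI z-score over 6 months". From these, "to achieve 80% power at an alpha of 0.05, we would need 64 children per group to complete the 6-month assessment". It also says: "We did not include a repeated measures correlation coefficient in our sample size calculation". No ICC, design effect or allowance for mentors appears anywhere in the article.

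**The concern.** Children whose parents share a mentor, a monthly meeting and a weekly coach are likely to have correlated outcomes. Because each mentor works in one arm, variation between mentors does not cancel in the positive deviance versus We Can! contrast but adds to its variance. The enrolment-period effect is common to both arms and cannot absorb variation between mentors within an arm. A child-level random effect, if one is fitted, handles only repeated measures on the same child.

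If mentor is left out, the standard error of the primary contrast is too small whenever the mentor ICC is positive. The Discussion says that the active comparator is there to show whether the content from the positive deviance inquiry works better. With few mentors per arm, a chance difference in mentor quality could be reported as an effect of that content. The sample size carries the same assumption of independence.

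**Working it through.** **Inputs from the article.** Difference 0.5, SD of change 1.0, alpha 0.05, power 80%, 64 completers and 80 enrolled per group, about 25% dropout (Sample size); up to 14 mentees per mentor per month (Parent mentor recruitment and training).

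**Assumed.** Mentor ICC 0.01, 0.02, 0.05 and 0.10, since the article gives none. Mean completed group sizes of 10 and 6, since 14 is a ceiling and no mean is stated. 80/14 = 5.7, so 6 concurrent mentors would cover an arm; with 60 completers that is 10 each. The second layout, 10 mentors of 6, has the same 60 completers in smaller groups.

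**Step 1: reproduce the plan's figure.** A two-sided, two-sample t-test with difference 0.5 and SD 1.0 needs 63.8, so 64 per group, and has 80.1% power at 64. A one-sided test needs 50 and does not match. The printed 64 is therefore the figure for independent children, with a design effect of 1.

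**Step 2: type I error if mentor is ignored.** With DE = 1 + (m − 1) × ICC, the error of a nominal 5% test is approximately 2 × [1 − Φ(1.96/√DE)]. For example, m = 10 and ICC 0.05 give DE = 1 + 9 × 0.05 = 1.45, 1.96/√1.45 = 1.63, and an error of 10.4%.

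| ICC | DE, m = 10 | Type I error | DE, m = 6 | Type I error |
|---|---|---|---|---|
| 0.01 | 1.09 | 6.0% | 1.05 | 5.6% |
| 0.02 | 1.18 | 7.1% | 1.10 | 6.2% |
| 0.05 | 1.45 | 10.4% | 1.25 | 8.0% |
| 0.10 | 1.90 | 15.5% | 1.50 | 11.0% |

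Simulated trials agree. With 6 mentors of 10 per arm, an unadjusted t-test rejects a true null in 6.0%, 7.1%, 10.3% and 15.8% of trials. With 10 mentors of 6 the range is 5.6% to 11.0%.

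**Step 3: power on the plan's own inputs.** Effective n = 64/DE, and power ≈ Φ(0.5 × √(n_eff/2) − 1.96). This approximation gives 80.7% at 64 independent children.

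| ICC | n_eff, m = 10 | Power | n_eff, m = 14 | Power |
|---|---|---|---|---|
| 0.01 | 58.7 | 77% | 56.6 | 76% |
| 0.02 | 54.2 | 74% | 50.8 | 71% |
| 0.05 | 44.1 | 65% | 38.8 | 60% |
| 0.10 | 33.7 | 54% | 27.8 | 46% |

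These figures carry no penalty for the small number of mentors.

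**Step 4: keep two other losses apart.** They should not be counted as clustering.
- *Dropout arithmetic.* 80 × 0.75 = 60 completers, not 64 (80 is 64 × 1.25, whereas 64/0.75 = 85.3, so 86). At 60 independent children the t-test has 77.5% power.
- *Degrees of freedom.* A test on mentor means with 6 mentors of 10 per arm has 10 degrees of freedom and 69.5% power even at ICC 0. Of the fall from 77.5% to 66% at ICC 0.01, 8 of 11.5 points come from the degrees of freedom and not from correlation.

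**The case against.** **The random effects are not listed.** The article says that mixed models will be used but names only fixed terms. It does not mention even the child-level effect that repeated measures would need. Its silence on mentor is therefore not a stated decision to leave mentor out, and an analysis plan could supply the term. This stands, and it limits the point to the model as described. It does not rescue the sample size, which is printed in the article.

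**The SD may be generous.** The baseline SD is 0.7, and 0.7 × √2 = 0.99, so an SD of change of 1.0 corresponds to almost no correlation between baseline and 6 months (taking equal SDs). If that correlation were 0.5, the SD of change would be 0.70, and even the mentor-level test with 6 mentors of 10 would have 92%, 90%, 83% and 73% power over the four ICCs. At a correlation of 0.25 it would have 79% to 55%. The article gives no correlation, just as it gives no ICC. This stands against any claim that the trial's actual power is below 80%. It does nothing for the type I error.

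**Groups may be small and mentors alike.** Fourteen is a ceiling, and recruitment runs across centers and enrolment periods. Shared training and selection of mentors on fidelity should also reduce differences between them. With 12 mentors of 5 the simulated type I error is 5.4% to 9.7%, and at ICC 0.01 the excess is negligible. This is fair on size. The direction is unchanged for any ICC above zero.

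**Conclusion.** The point holds in conditional form. The design nests mentors within both arms of the primary comparison, the model as described has no term for them, and the sample size treats children as independent. For any positive mentor ICC the described Wald test is liberal: about 6% to 16% with 6 mentors of 10 completers per arm, and about 5.6% to 11% with 10 of 6, over an assumed ICC of 0.01 to 0.10. With difference 0.5, SD 1.0 and 64 completers, the stated 80% power holds only at ICC 0. It is about 77% to 54% with groups of 10.

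A reader might infer two stronger things: that the primary test is certainly invalid, and that the trial will not have 80% power. The documents support neither. The first needs a positive ICC and confirmation that no mentor term is fitted. The second needs the true SD of change and the baseline correlation, which could offset the loss.

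This should be fixed before outcomes are analysed. It is not rated as a fatal fault, because its size rests on an ICC and a mean group size that the article does not give.

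**What to change.** - **Data:** record the mentor (and mentoring group) ID for every mentee. Mentees are assigned to mentors and mentors are paid per mentee, so the link very likely exists already.
- **Model:** in the primary and secondary analyses, add a random effect for mentor in the two mentored arms, as a partially nested model with each usual-care dyad as its own cluster. Place it on change from baseline. If baseline is modelled as a repeated outcome, use a mentor-by-time effect, because a mentor intercept alone would leave between-mentor variation in change inside the group-by-time test.
- **Test:** replace large-sample Wald tests with Satterthwaite or Kenward-Roger type degrees of freedom.
- **Sample size:** restate power over a stated ICC range and an expected mean group size, with the assumed SD of change justified. Report the shortfall of 60 against 64 completers as a separate item.

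The cost is plan wording and one ID variable, with no added enrolment. In return the confidence intervals widen and the stated power looks less favourable. Restating power does not restore it.

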### Outcome measures

#### Primary outcome

The primary outcome is change in adjusted BMI z-score at the end of the active intervention period, 6 months post-enrollment. Adjusted BMI z-scores account for child age and gender and allow the evaluation of changes in BMI z-scores within the upper range of z-scores expected during this trial [28]. Adjusted BMI z-score is assessed in all three arms. The primary comparison is between the two active intervention groups at 6 months. The 12-month time point serves as an evaluation of maintenance of any changes post-intervention (Fig. 3).

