#### Secondary outcomes

Blood pressure, waist circumference, self-efficacy, feeding practices, dietary intake, physical activity, sleep, and screen time are assessed by interviewer-administered survey at baseline, at end of the 6-month intervention period, and at the 12-month time point in all three intervention arms. The home food environment assessment is completed only in intervention and active control dyads at baseline and 4-month follow-up.

Blood pressure and waist circumference: Trained research personnel obtain blood pressure readings on child participants by using a standardized sphygmomanometer (model CONTEC08A, Contec Medical Systems, Qinhuangdao, China) on both arms in duplicate for each arm, as tolerated, and the mean of both values for each arm is used. Waist circumference is obtained by using the anterior superior iliac crest and umbilicus as anatomic landmarks, in triplicate with the mean of two measurements within 1 cm recorded or the mean of all three values if equally spaced.

Self-efficacy: The Generalized Self-Efficacy Scale (GSES) (12 items) [29, 30] is administered as well as parental self-efficacy questions related specifically to diet and physical activity practices and behaviors [31]. The GSES ranges from a score of 12 to 60 (higher scores indicate greater self-efficacy), and domains of initiative, persistence and effort are examined as subscales. The GSES has good internal consistency; Cronbach’s alpha values are 0.86 for the overall scale and 0.77–0.83 for the subscales [30]. The parental self-efficacy questions had been developed and tested previously among parents of preschool children, and the overall scale had a Cronbach’s alpha of 0.94 [31]. We added two questions on self-efficacy related to consistency in rules around snacking and communication with other providers; although we collected feedback from representative parents on these questions, these two queries have not otherwise been validated.

Comprehensive Feeding Practices Questionnaire (CFPQ) subscales: The intervention targets the food environment and potentially influences parental monitoring and control. Thus, we administer three subscales of the CFPQ to parents (environment, monitoring, and control subscales) [32]. The CFPQ is composed of a five-point, Likert-like scale ranging from “never” to “always” on responses related to practices and has a continuous outcome.

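### The mediators are defined as the secondary outcomes, which include waist circumference and blood pressure, so a second measure of adiposity could be reported as mediating the effect on adiposity

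*Protocol article*

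**What the plan says.** The mediation paragraph in Data analysis (protocol article) reads: "We will employ three regression equations to complete planned mediation analyses of intervention effects by the secondary outcomes". The second of the three equations estimates "the main intervention effect on the mediating variables (secondary outcomes", the closing words standing in parentheses as the definition of the mediators. The method follows: "We will use a product-of-coefficients approach to examine the potential mediators".

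The set meant is given under Secondary outcomes: "Blood pressure, waist circumference, self-efficacy, feeding practices, dietary intake, physical activity, sleep, and screen time are assessed", with timing "at baseline, at end of the 6-month intervention period, and at the 12-month time point in all three intervention arms". The same section adds: "The home food environment assessment is completed only in intervention and active control dyads at baseline and 4-month follow-up".

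The dependent variable is fixed under Primary outcome: "The primary outcome is change in adjusted BMI z-score at the end of the active intervention period, 6 months post-enrollment".

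**The concern.** Mediation analysis here should show which parental behaviours and beliefs carry an effect on the child's weight. The Experimental arm design section sets out that chain: personal determinants such as self-efficacy lead to small component behaviours, these to four core parent behaviours, and these to weight. Waist circumference has no place on that chain. It is a second reading of the endpoint. Blood pressure does not measure adiposity, but it more plausibly follows weight change than causes it.

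By defining mediators through the label of secondary outcome, the plan admits both. Product of coefficients cannot detect the error. It needs only an arm difference on the candidate and a within-arm association between candidate and outcome, and it gives the same answer whichever way causation runs. At stake is the account of mechanism: a waist result could outrank the behaviours that the curricula target.

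**Working it through.** **The plan's own figure.** The mediation plan states no number. The related figure is 64 completers per group (Sample size section), from a difference of 0.5, SD 1.0, alpha 0.05 (two-sided assumed) and 80% power.

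- Normal approximation: n = 2 × (1.96 + 0.8416)² × 1.0² / 0.5² = 62.8, so 63.
- Exact t calculation: power is 0.795 at 63 and 0.801 at 64. The stated 64 is reproduced.

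**Inputs for the illustration.** From the Sample size section: arm effect c = −0.5 on the outcome Y, SD 1.0, 64 per arm, two arms. Assumed, because the article gives no value: r, the within-arm correlation of the candidate M with Y. M is scaled to SD 1.

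**Formulas.**

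- Path a is the arm effect on M. Path b is the coefficient of M in the regression of Y on arm and M. With unit SDs, b = r.
- Apparent share mediated = a × b / c = r × (a / c).
- Case 1, M merely tracks Y (M = rY + noise, no path from M to Y): a = r × c, so the share is r².
- Case 2, equal arm effects on M and Y in SD units: a = c, so the share is r.

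**Results.** The true mediated effect is zero throughout. The last three columns refer to case 1; the last two come from 3,000 simulated trials per row.

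| r | Share, case 2 (r) | Share, case 1 (r²) | a × b by formula | Share, simulated | Both paths significant |
|---|---|---|---|---|---|
| 0.2 | 20% | 4% | −0.10 × 0.2 = −0.020 | 4% | 5.5% |
| 0.3 | 30% | 9% | −0.15 × 0.3 = −0.045 | 9% | 12.5% |
| 0.5 | 50% | 25% | −0.25 × 0.5 = −0.125 | 25% | 29% |
| 0.7 | 70% | 49% | −0.35 × 0.7 = −0.245 | 49% | 51% |
| 0.8 | 80% | 64% | −0.40 × 0.8 = −0.320 | 64% | 63% |
| 0.9 | 90% | 81% | −0.45 × 0.9 = −0.405 | 81% | 71% |

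For any other ratio of arm effects, the share scales with a / c. For example, an arm effect on waist half that on BMI z-score, in SD units, gives r / 2.

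**The case against.** The strongest defence is that a condensed article need not name every mediator. The abstract's examples of secondary outcomes are behavioural and psychosocial, the intervention was built on a behavioural pathway, and the text speaks only of potential mediators. A sensible analyst might never fit the waist model. This stands in part: the article does not say that every secondary outcome will be interpreted as a mediator. But the abstract's list is given as examples, and potential mediators names no subset. The article does not leave the set open for another document. It defines the set, and the definition takes in both physical measures.

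Several stronger readings are tempting and are not supported:

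- **A large indirect effect for blood pressure.** The article gives no correlation for it, and under case 1 a weak one (r of 0.2 to 0.3) gives only 4% to 9%.
- **A mediated share of 70% to 90% for waist.** This needs both equal arm effects in SD units and r of 0.7 to 0.9, neither of which the article states.
- **Waist would certainly be the strongest mediator.** That depends on r and on an arm effect existing. Even at r = 0.9, both paths reach significance in only about 71% of simulated trials under case 1.
- **Home food environment cannot be used because usual care has no data.** The article specifies no three-arm mediation regression. The primary comparison is between the two mentor arms, where this measure is taken, and its 4-month assessment precedes the 6-month outcome.
- **Mediators and outcome must come from the same visit.** Most candidates share the 6- and 12-month visits with BMI, but the mediation paragraph fixes no time points, so lagged models remain open.

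**Conclusion.** The point holds as a flaw in a stated rule. Followed as written, the plan would test waist circumference, a second measure of the same adiposity, as a mediator of the adiposity effect. It would also test blood pressure, for which the problem is probably smaller. A spurious indirect effect for waist could be about 25% to 81% of the total effect if waist merely tracks BMI z-score and r lies between 0.5 and 0.9, or equal to r if the standardised arm effects are equal. The size rests entirely on the assumed r, the assumed relation between the two arm effects, and the planning effect of 0.5 with SD 1.0 being real.

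The consequence is limited to the interpretation of mechanism. The primary comparison, its alpha and the 64 completers per group do not change.

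**What to change.** In the mediation paragraph of Data analysis, replace the general reference to secondary outcomes with a named list: self-efficacy, feeding practices, dietary intake, physical activity, sleep, screen time and, for the contrast between the two mentor arms where it is measured, home food environment. State that waist circumference and blood pressure are analysed as outcomes only. This is a one-sentence change. It needs no new data, and both physical measures keep their place in the secondary analysis.

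Optionally, add a sensitivity analysis of the 6-month mediator on 12-month adjusted BMI z-score, adjusting for 6-month BMI z-score as well as baseline values of mediator and outcome. Without the 6-month BMI term, the lag would not deal with reverse causation. The cost is fewer completers, and the question shifts to maintenance, which is how the article describes the 12-month visit. It should supplement the main mediation analysis, not replace it.
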